#### Primary outcome

2.11.2

The primary outcome between follow‐up and fluid bolus groups will be adjusted for the two stratification variables^25^ (presence of AKI and presence of sepsis) using two‐tailed logistic regression. Obtained odds ratios (OR) will be converted to risk ratios (RR) with 95% confidence intervals (CI). Additionally, we will report crude event rates and risk ratios.

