### Randomization

2.4

Eligible patients will be randomized 1:1 within 1 hour of full eligibility using computer‐based algorithm created by an independent statistician and web‐based allocation concealment for randomization. Randomization is stratified according to the presence/absence of AKI (defined by KDIGO criteria^4^) and sepsis (according to the Sepsis definition^18^). Permutated blocks of varying size (4, 6, or 8) are used.

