#### Secondary and exploratory outcomes

2.11.3

As the primary outcome, the secondary and exploratory outcomes will be adjusted for the two stratification variables.^25^ Continuous measures will be expressed according to their distribution and difference between the groups in the change in individual urine output, duration of consecutive oliguria, and cumulative fluid balance on study day will be compared using mean or median regression depending on normal distribution and expressed with 95% CIs. Dichotomous endpoint measures (number of patients receiving rescue boluses, highest AKI stage within 24, 48 hours and during ICU stay, and number of patients receiving RRT) will be analyzed using ordinal or logistic regression and reported as risk ratios with 95% CIs. Furthermore, crude event rates and risk rations will be reported for dichotomous outcomes and absolute differences with 95% CIs for continuous outcomes.

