### Sample size

2.12

No reliable previous data to inform about the incidence of the primary outcome were available. Among oliguric (urine output <0.5 mL/kg/h for at least 3 hours), hemodynamically stable patients, 50% were considered as renal responders to a fluid challenge that constituted at least one 500 mL crystalloid bolus administered over 15 minutes.^10^ In that study the definition of a positive renal response (post‐bolus urine output over 0.5 mL/kg/h for at least 3 hours) was more liberal than in our trial.^10^ Fluid bolus did not significantly increase urine output among patients with acute respiratory distress syndrome (both oliguric and non‐oliguric).^5^ Therefore, we assume that 30% of patients in the fluid bolus group will be endpoint‐positive. Additionally, we consider 20% absolute difference (which translates to a number needed to treat of 5) as a minimum clinically meaningful difference between the groups to support the use of such a common and inexpensive intervention. Thus, to reach a 20% absolute difference in the primary outcome (30% in the fluid bolus group and 10% in the noninterventional follow‐up group), 62 patients per group will be required to reach 80% power with significance level set at .05 (two‐sided). Considering possible drop‐outs we aim to randomize 65 patients per group to target at least 62 patients per group in the ITT population.

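### Converting the adjusted odds ratio to a risk ratio leaves the primary confidence interval open to a wrong width that depends on the reference arm; estimating the risk ratio from the model avoids this

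*Protocol article*

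**What the plan says.** Section 2.11.2 (Primary outcome) compares the proportion of responders by logistic regression adjusted for the two stratification variables, AKI and sepsis. It continues: "Obtained odds ratios (OR) will be converted to risk ratios (RR) with 95% confidence intervals (CI"). Crude event rates and crude risk ratios are reported alongside. Section 2.11.3 (Secondary and exploratory outcomes) sends the dichotomous outcomes through logistic or ordinal regression, to be "reported as risk ratios with 95% CIs".

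Neither section names the conversion formula, the baseline risk that enters it, the reference arm, or the way the interval is built.

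The design figures are in section 2.12 (Sample size): "30% in the fluid bolus group and 10% in the noninterventional follow"-up group, and "62 patients per group will be required to reach 80% power with significance level set at .05" (two-sided).

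The article's labels do not settle the reference arm. The abstract calls follow-up experimental and the bolus control, and section 2.7.2 calls the bolus group standard. Section 2.12, however, treats follow-up as the lower baseline and the bolus as the treatment to be supported: "we consider 20% absolute difference (which translates to a number needed to treat of 5").

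**The concern.** The wording starts from the odds ratio. The usual way to turn an odds ratio into a risk ratio is the closed form RR = OR / (1 − P0 + P0 × OR), applied to the estimate and to both limits, where P0 is the observed risk in the reference arm. This treats P0 as known. Here P0 would come from about 62 patients and, if follow-up is the reference, from about six events (0.10 × 62 = 6.2). The interval leaves that uncertainty out. The formula is also not symmetric in the two arms, so the limits for A/B are not the reciprocals of the limits for B/A.

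With responder rates of 10% to 30%, odds ratio and risk ratio differ too much for this to be negligible. At stake is the stated precision of the adjusted primary estimate. That precision matters in a trial whose hypothesis is that the groups do not differ to a clinically significant degree, because such a reading leans on the confidence limits as well as the P value.

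**Working it through.** **Inputs from the article.** Responders 30% (bolus) and 10% (follow-up), 62 per arm, two-sided 0.05, 80% power (section 2.12); logistic model with AKI and sepsis (section 2.11.2).

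**Inputs assumed.** The closed-form conversion; for the simulations, AKI and sepsis prevalence of 50% each, with log odds ratios of −0.5 and −0.3.

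**1. The plan's own figure.** With pooled variance and no continuity correction,
n = [1.96 × √(2 × 0.20 × 0.80) + 0.8416 × √(0.30 × 0.70 + 0.10 × 0.90)]² / 0.20² = (1.109 + 0.461)² / 0.04 ≈ 61.6, rounded up to 62. The stated figure is reproduced; power at 62 per arm is 80.3%.

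**2. Odds ratio at the planned rates.** Expected cells are 18.6 and 43.4 (bolus), 6.2 and 55.8 (follow-up).
- OR = (0.30/0.70) / (0.10/0.90) = 3.86
- SE(log OR) = √(1/18.6 + 1/43.4 + 1/6.2 + 1/55.8) = 0.506
- 95% CI 1.43 to 10.40

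**3. Conversion with follow-up as reference (P0 = 0.10).**
- Lower: 1.431 / (0.9 + 0.1431) = 1.37
- Upper: 10.398 / (0.9 + 1.0398) = 5.36
- RR 3.00 (1.37 to 5.36), log width 1.36

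**4. Conversion with bolus as reference (P0 = 0.30).** The follow-up/bolus odds ratio has limits 1/10.398 = 0.0962 and 1/1.431 = 0.699.
- Lower: 0.0962 / (0.7 + 0.0289) = 0.132
- Upper: 0.699 / (0.7 + 0.2097) = 0.768
- RR 0.333 (0.132 to 0.768); inverted to bolus/follow-up, 3.00 (1.30 to 7.58), log width 1.76

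**5. Direct log-RR interval.** SE = √(1/18.6 − 1/62 + 1/6.2 − 1/62) = 0.428, giving 3.00 (1.30 to 6.94), log width 1.68. Relative widths are 1.363/1.676 = 0.81 (19% too narrow) and 1.762/1.676 = 1.05 (5% too wide).

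With whole counts (19/62 vs 6/62) the pattern is the same: 1.44 to 5.64, or 1.36 to 8.08, against 1.36 to 7.39 directly.

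**6. Equal rates, 20% vs 20%.** The odds ratio limits are 0.415 and 2.411. They convert to 0.47 to 1.88 with follow-up as reference and, inverted, to 0.53 to 2.13 with bolus as reference; the direct interval is 0.49 to 2.02. Log width is 1.387 against 1.408, within 1.5% of direct for either reference, but the limits still move.

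**7. Coverage under the adjusted model** (2,500 simulated trials per scenario, 62 per arm, nominal 95%).

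| True rates, bolus vs follow-up | Converted, follow-up reference | Converted, bolus reference | Marginal standardisation |
|---|---|---|---|
| 30% vs 10% | 90.7% | 97.5% | 96.4% |
| 30% vs 30% | 95.5% | 95.5% | 95.8% |
| 20% vs 20% | 94.6% | 94.6% | 95.1% |

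The Monte Carlo error near 91% is about √(0.907 × 0.093 / 2500) = 0.6 percentage points. Further runs with other covariate assumptions keep the 30% vs 10% figures at about 91 to 92% and 97 to 98%. With log odds ratios of −0.7 and −0.5, modified Poisson covers 95.2 to 96.2% across three scenarios with a 20-point difference. At 25% vs 15% the converted intervals cover 93.8% and 96.3%.

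**8. Significance.** The conversion is increasing in OR and equals 1 exactly when OR = 1. The converted limits therefore exclude 1 exactly when the odds ratio limits do.

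**The case against.** The strongest objection is that the article names no formula. A conversion through model-predicted risks, with a delta-method or bootstrap interval, would have neither fault, and such detail is often left to a full analysis plan that is not shown here. This stands in part. It rules out saying that the published interval will be wrong, which a reader might infer from the calculation. It does not remove the point, because the article does state a step that takes the odds ratio as its input, and the closed form is the natural reading of that step.

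Second, the under-coverage arises only with follow-up as reference, whereas the arm labelled control is the bolus, which gives the conservative case. This stands. The labels do not fix the model's reference level, however, and the sample size section reasons from follow-up as baseline.

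Third, no decision at the 5% level changes, the clinically meaningful difference is an absolute one, and crude risk ratios are reported too. All true, and it limits the severity. The crude ratio is still not the adjusted primary estimate.

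Fourth, a reader might think that putting a marginal baseline risk into a conditional odds ratio is a serious fault of its own. It is not: with covariate effects set to zero, coverage at 30% vs 10% is 90.6% and 97.4%, essentially unchanged.

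Fifth, the size for the outcomes in section 2.11.3 cannot be given, since the article states no expected rates for them. If they are rare, odds ratio and risk ratio nearly coincide.

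**Conclusion.** The point holds conditionally. If the closed-form conversion is used, the adjusted risk ratio at the design rates carries an upper limit of 5.36 or 7.58 from the same data, depending only on the coding, against 6.94 directly. The discrepancy shrinks with the true difference; under equal rates coverage is right and only the placement of the limits shifts.

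Two stronger readings are not supported. The first is that the primary interval will be too narrow: this needs both an unnamed formula and a reference arm that the control label does not suggest. The second is that the primary conclusion is compromised: the test, the sample size and the power are untouched. What is affected is the reported precision of one estimate. Severity is minor to moderate and confidence moderate. The coverage figures rest on assumed AKI and sepsis prevalences and effects; the limits in steps 2 to 6 of the check are unadjusted and need only the planned rates and the formula.

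**What to change.** Replace the conversion sentence in section 2.11.2. Keep the adjusted logistic model and obtain the risk ratio by marginal standardisation: average the predicted risks with every patient set to each arm in turn, and take the interval from the delta method or a bootstrap. Report the risk difference from the same step, because the trial's meaningful difference is 20 percentage points. Modified Poisson regression with robust variance, adjusted for AKI and sepsis, is an equally acceptable route to the risk ratio. With either method the ratio and its interval simply invert when the reference changes.

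State which arm is the reference, and use the same method for the binary outcomes in section 2.11.3. If an analysis plan that is not shown already specifies this, aligning the article's sentence with it is enough.

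The cost is a few lines of code and a sentence or two of text. If follow-up would have been the reference, the reported interval becomes somewhat wider: at 30% vs 10% the mean simulated log width is 1.44 for the converted interval and 1.77 for marginal standardisation.

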#### Secondary and exploratory outcomes

2.11.3

As the primary outcome, the secondary and exploratory outcomes will be adjusted for the two stratification variables.^25^ Continuous measures will be expressed according to their distribution and difference between the groups in the change in individual urine output, duration of consecutive oliguria, and cumulative fluid balance on study day will be compared using mean or median regression depending on normal distribution and expressed with 95% CIs. Dichotomous endpoint measures (number of patients receiving rescue boluses, highest AKI stage within 24, 48 hours and during ICU stay, and number of patients receiving RRT) will be analyzed using ordinal or logistic regression and reported as risk ratios with 95% CIs. Furthermore, crude event rates and risk rations will be reported for dichotomous outcomes and absolute differences with 95% CIs for continuous outcomes.

#### Other variables

2.11.4

Continuous variables will be compared with Mann‐Whitney *U *test or Student's *t* test depending on normal distribution, and categorical data using Chi‐squared test.

#### Missing data

2.11.5

We do not expect to have missing data about the primary outcome measure or stratification variables in the ITT population. Regarding secondary or exploratory outcomes, some missingness is expected (for example CVP values in patients who have not a central line inserted), but imputation will not be used. Regarding other data points, if the amount of missing observations regarding other variables is less than 5%, we do not impute data. Regarding descriptive data, an appropriate multiple imputation strategy according to the type of missingness (missing at random or missing completely at random) will be used if missingness exceeds 5% of observations.

### Sample size

2.12

No reliable previous data to inform about the incidence of the primary outcome were available. Among oliguric (urine output <0.5 mL/kg/h for at least 3 hours), hemodynamically stable patients, 50% were considered as renal responders to a fluid challenge that constituted at least one 500 mL crystalloid bolus administered over 15 minutes.^10^ In that study the definition of a positive renal response (post‐bolus urine output over 0.5 mL/kg/h for at least 3 hours) was more liberal than in our trial.^10^ Fluid bolus did not significantly increase urine output among patients with acute respiratory distress syndrome (both oliguric and non‐oliguric).^5^ Therefore, we assume that 30% of patients in the fluid bolus group will be endpoint‐positive. Additionally, we consider 20% absolute difference (which translates to a number needed to treat of 5) as a minimum clinically meaningful difference between the groups to support the use of such a common and inexpensive intervention. Thus, to reach a 20% absolute difference in the primary outcome (30% in the fluid bolus group and 10% in the noninterventional follow‐up group), 62 patients per group will be required to reach 80% power with significance level set at .05 (two‐sided). Considering possible drop‐outs we aim to randomize 65 patients per group to target at least 62 patients per group in the ITT population.

### Pre‐planned subgroup analyses

2.13

The primary and secondary outcome measures will be analyzed in two pre‐defined subgroups: (a) patients with sepsis according to sepsis‐3 definition^18^ and (b) patients with AKI defined by the KDIGO criteria.^4^ Presumably, patients with AKI may exert a poorer response in terms of urine output to fluid bolus than those without AKI. Additionally, the recent pathophysiological hypotheses regarding oliguria in sepsis suggest that oliguria may be an adaptive mechanism to severe inflammation,^26^ suggesting also a lower incidence of reversal of oliguria. The results obtained in the subgroups will be interpreted as hypothesis generating and heterogeneity between subgroups will be assessed by *I*
^2^‐test.

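### Subgroup heterogeneity is to be judged by an I²-test, but I² is a descriptive index with no P-value or error level, and the contrast it applies to is left unclear

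*Protocol article*

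**What the plan says.** Section 2.13 (Pre-planned subgroup analyses) of the protocol article states: "The primary and secondary outcome measures will be analyzed in two" subgroups named in advance, namely patients with sepsis and "patients with AKI defined by the KDIGO criteria". The reason given for the second is that "patients with AKI may exert a poorer response in terms of urine output to fluid bolus than those without AKI". The section closes by saying "The results obtained in the subgroups will be interpreted as hypothesis generating" and that "heterogeneity between subgroups will be assessed by" an I²-test. It gives no I² cut-off, no Q statistic and no interaction term.

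Two other places bear on this. Section 2.4 (Randomization) says "Randomization is stratified according to the presence/absence of AKI" and likewise by sepsis, so these are two separate yes/no factors. Section 2.11.2 (Primary outcome) has the treatment comparison "adjusted for the two stratification variables" by logistic regression, so both factors are already in the model as main effects. Section 2.11.1 sets significance at .05 with two-sided P-values.

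**The concern.** The section fixes a method by name, and that method cannot do what is asked of it. I² comes from meta-analysis, where it describes the share of variation between independent study estimates that exceeds chance. It produces no P-value, so it cannot be read against the .05 level in section 2.11.1. With no cut-off stated, the criterion for calling the subgroups different is open until the data are seen.

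The wording also does not settle what is compared. The two groups listed are sepsis patients and AKI patients, and a patient could belong to both. The AKI hypothesis, however, sets AKI against no AKI. These contrasts differ, and the index behaves differently under each.

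At stake is whether the pre-planned statement about a weaker response in AKI is judged on a defined quantity. Nothing in the primary analysis depends on it.

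**Working it through.** **Inputs.** From the article: two subgroups and the I²-test (section 2.13); two separate stratification factors (2.4); both factors in the logistic model (2.11.2); 30% vs 10% responders, 62 per group, 80% power, two-sided .05 (2.12). Assumed, because the article gives no figure: the I² cut-offs, the prevalence of each factor (30%, 50%, 70%) and any overlap between sepsis and AKI.

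**1. The plan's own figure.** Section 2.13 has no number to reproduce, but the simulations use the planned size, so that was checked first. With pooled variance and mean proportion 0.20:

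n = [1.96·√(2·0.20·0.80) + 0.842·√(0.30·0.70 + 0.10·0.90)]² / 0.20² = (1.109 + 0.461)² / 0.04 ≈ 61.6, so 62 per group, as stated. Power at 62 is 80.3%.

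**2. I² with two groups.** I² = max(0, 1 − df/Q). With two groups df = 1, so I² = 1 − 1/Q when Q > 1, and I² > c is the same event as Q > 1/(1 − c). With independent groups and no true heterogeneity, Q follows a chi-square on 1 df in large samples:

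| I² exceeds | Q exceeds | Probability |
|---|---|---|
| 0 | 1.00 | 31.7% |
| 25% | 1.33 | 24.8% |
| 50% | 2.00 | 15.7% |
| 75% | 4.00 | 4.6% |

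Conversely, the 5% critical value Q = 3.84 gives I² = 1 − 1/3.84 = 74%.

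**3. At this trial's size.** The two levels of one factor were simulated with 62 per arm and 30% vs 10% in both levels (a common odds ratio). Q was computed from the difference in log odds ratios.
- I² > 50% occurred in 11.7%, 12.7% and 11.6% of trials at prevalences of 30%, 50% and 70%, so about 12-13%.
- The nominal 5% Q test rejected in about 2.5%, because it is conservative with small cells.

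**4. When the effect does differ.** With 30% vs 10% in one level and 10% vs 10% in the other, median I² was 19%, 32% and 20% at the three prevalences. I² > 50% occurred in 37-41% of trials. The index would therefore often look low when the bolus works in one level only. The 1-df test itself had power of 14.9%, 18.6% and 13.9%.

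**5. If sepsis patients are compared with AKI patients.** Take equal subgroup sizes, a share r of patients in both, and a common effect. The true variance of the difference is then (1 − r) times the one Q assumes, so P(Q > 3.84) becomes P(χ² > 3.84/(1 − r)) with 1 df:
- r = 25%: 2.4%
- r = 50%: 0.6%
- r = 75%: 0.01%

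The same overlaps take the chance of I² > 50% from 15.7% to 10.2%, 4.6% and 0.5%. Overlap makes the statistic conservative.

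**The case against.** The strongest defence is that I²-test is shorthand for the heterogeneity test usually printed beside I². For the two levels of one factor, that test is Cochran's Q on 1 df, equivalent to an interaction test, and I² loses no information because it is a transform of Q. On that reading only the label is at fault. This is plausible, but the section mentions neither Q nor a P-value, so the reading cannot be confirmed from the text.

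The defence is right on several other points, and they limit what can be claimed:
- A reader might infer that the plan will flag heterogeneity far too often. The documents do not support this, because it depends on cut-offs that the protocol never states. The 16% is a large-sample value that falls to about 12-13% at this trial's size.
- A reader might infer that overlapping subgroups are an established flaw that adds to false flags. Overlap is only inferred from the two-factor design, and its extent is unknown. It arises only if sepsis patients are compared with AKI patients, and it would then reduce false flags. If each factor's presence is compared with its absence, there is no overlap.
- A reader might infer that septic patients are predicted to respond less to the bolus. Section 2.13 says that oliguria in sepsis may reverse less often, which could be a statement about prognosis.
- The results are labelled hypothesis generating, section 2.11.1 bases the conclusions on the ITT analysis, and the trial is a pilot.

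That label lowers the stakes but does not supply the missing criterion. An analysis plan that is not shown might say more, but the method named here would still need correcting.

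**Conclusion.** The point holds as one about a wrongly chosen method and an unclear contrast. I² supplies no P-value or error level. With two groups it is unstable in both directions: under a conventional 50% cut-off (assumed), it would be exceeded in about 16% of homogeneous trials in theory and 12-13% in simulation, while its median is only 19-32% when the effect is confined to one level. These figures assume non-overlapping groups; the simulated ones also assume the section 2.12 response rates and factor prevalences of 30-70%. Under a sepsis-versus-AKI comparison the statistic would be conservative to an unknown degree.

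The consequence is modest. It is confined to exploratory subgroup statements and leaves the primary analysis, its conclusions and the 62 per group untouched. It is still worth correcting, because the subgroups are pre-planned and the stated AKI question has a direct answer in the model already specified.

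**What to change.** In section 2.13, replace the I²-test with a treatment-by-AKI interaction term and, in a separate model, a treatment-by-sepsis interaction term. Add each to the primary logistic model and to the regressions for the secondary outcomes. Report the interaction estimate with its 95% CI and P-value, and the treatment effect in each level: AKI and no AKI, sepsis and no sepsis. This also settles which groups are compared.

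Keep the hypothesis-generating label, and add that power for interaction is low (about 14-19% under the assumptions above). A non-significant interaction should then not be read as evidence of a uniform effect, and the interval should carry the interpretation.

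The cost is a sentence or two of analysis wording. No new data, patients or changes to the primary analysis are needed.
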